#### Intervention in control group

To examine the efficacy of the intervention in the control group, changes in outcome measures between T0 and T1 (usual care) will be compared with the changes in outcome measures between T1 and T2 (intervention) using a paired samples *T*-test.

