## Methods/design

### Study design

The current study is a multi-center (4 sites) randomized controlled trial, with the control group also entering the training arm directly following completion of the initial protocol. After randomization (1:1), subjects in both groups will perform a test battery of exercise tests, questionnaires, and other measurements (see study outcomes) (T0 measurement). Thereafter, subjects in the intervention group will receive an exercise training regimen, while the subjects in the control group will continue to receive standard care over a 12-week period. Subsequently, subjects in both groups will repeat the battery of tests from T0 (T1 measurement). Subjects in the intervention group will then receive individual advice based on their T1 results and educated on the physical activity guidelines for children [20] in order to help maintain fitness levels following the intervention. Subjects in the control group will enroll in the exercise training program. Following this 12-week period, subjects in both groups will repeat the battery of tests from T0 and T1 (T2 measurement) and the subjects in the control group will receive individual feedback in the same manner as the intervention group at T1. After 12 weeks, the subjects in the control group will repeat the battery of tests from T0, T1, and T2 (T3 measurement). See Figure1 for a flow diagram of the study design.

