### Baseline description of groups

The baseline descriptors of the groups are age, gender, anthropometrics and disease characteristics. The anthropometrics include maturity offset (years), height (M), body mass (kg), body mass index (kg·m^-2^), and fat free mass (kg). The disease characteristics include age at diagnosis (years), disease duration at inclusion (years), disease course (monocyclic/ polycyclic/ chronic), and medication usage. These descriptors will be compared between the treatment group and the control group at T0. Maturity offset will be determined with gender-specific equations including chronological age, height, body mass, and sitting height [31]. Fat free mass will be measured with BODYSTAT® QuadScan 4000. Disease duration at inclusion will be defined as the time from diagnosis to inclusion. Disease course will be classified as monocyclic (no signs of disease activity 2 years after diagnosis), polycyclic (recurrence of active disease after a definite remission (>6 months), followed by one or more flares), or chronic (persistent disease activity >2 years after diagnosis)[32].

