#### Intervention group Vs control group

To examine the efficacy of the intervention, the outcome measures of the intervention group and control group will be compared at each of time points T0 and T1 using mixed linear regression analysis with group (intervention/control) as independent variable and the outcome measures (see Table2) as separate dependent variables.

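### The control-group analysis is given an efficacy aim, but it is a non-randomised, fixed-order contrast in which training cannot be separated from anything else that differs between the two 12-week windows

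*Protocol article*

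**What the plan says.** The statistical section of the protocol article lists three types of analysis and does not rank them.

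- **Randomised comparison** (*Intervention group Vs control group*): to examine efficacy, "the outcome measures of the intervention group and control group will be compared at each of time points T0 and T1" by mixed linear regression.
- **Control group only** (*Intervention in control group*): the aim is "To examine the efficacy of the intervention in the control group", and "changes in outcome measures between T0 and T1 (usual care) will be compared with the changes in outcome measures between T1 and T2 (intervention" phase), "using a paired samples *T*-test".
- **Decision rule**: the closing paragraph, printed under the wash-out heading but worded for results in general, calls a result significant when its 95% confidence interval excludes the null value.

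*Study design* fixes the order. In the first window "subjects in the control group will continue to receive standard care over a 12-week period". After T1, "Subjects in the control group will enroll in the exercise training program". Over the same second window the other arm has finished training: "Subjects in the intervention group will then receive individual advice based on their T1 results".

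**The concern.** The second analysis has the same kind of aim as the randomised comparison, and no different decision rule is given for it. It does not have the same protection. No control trains first, so within this group training and window are the same variable. The intervention arm is already trained and advised during T1–T2, so it cannot show what that window does without training.

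The document gives reasons why the two windows might differ. Patients are selected at entry on recent relapse and on exercise limitation (*Subjects*), and that selection acts just before T0 only. The treadmill test ends at voluntary exhaustion, so familiarity may matter, and the first retest falls in the usual-care window. The disease course need not be linear: one of the baseline categories is "polycyclic (recurrence of active disease after a definite remission (>6 months), followed by one or more flares".

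If a significant result here is reported as efficacy, a window effect could be taken for a training effect. A null result could equally come from a window effect that masks one.

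**Working it through.** **Inputs.** The plan attaches no figure to this analysis, so there is none to reproduce. From *Power calculation*: mean VO2peak/kg 33, SD 8, target 22%, so 0.22 × 33 = 7.26 ml/kg/min. Planned total 30 at 1:1, so about 15 controls. The correlation r between visits is not given. I assume it is equal for all pairs of visits, with the same SD at each visit, and take r from 0.5 to 0.9.

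**1. The contrast.** (T2 − T1) − (T1 − T0) = T2 − 2·T1 + T0.

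**2. What it picks up with no training effect** (mean shifts in ml/kg/min, illustrative):

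| Pattern at T0, T1, T2 | Contrast |
|---|---|
| Steady drift: 0, 1, 2 | 2 − 2 + 0 = 0 |
| One-off learning at first retest: 0, 2, 2 | 2 − 4 + 0 = −2 |
| Gain only in T1–T2: 0, 0, 2 | 2 − 0 + 0 = +2 |
| Group-wide dip at T1: 0, −2, 0 | 0 + 4 + 0 = +4 |
| Group-wide peak at T1: 0, 2, 0 | 0 − 4 + 0 = −4 |

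**3. Precision.** The variance is (1 + 4 + 1)σ² + 2rσ²(−2 + 1 − 2) = 6σ²(1 − r) per child. With n = 15 and σ = 8, the standard error is 8·√(6(1 − r)/15): 3.58 at r = 0.5, 2.26 at r = 0.8 and 1.60 at r = 0.9.

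**4. Effect on the paired t-test** (noncentral t, 14 degrees of freedom, two-sided 5%):

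| r | Rejection with no training effect, net +2 | Power for 7.26, no window effect | Power for 7.26, net −2 |
|---|---|---|---|
| 0.5 | 8.2% | 47.2% | 27.8% |
| 0.8 | 13.1% | 84.7% | 58.1% |
| 0.9 | 21.4% | 98.8% | 86.3% |

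**5. Overlap with the randomised comparison**, both effects null, n per arm:

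- Against the between-arm difference in change: covariance 3(1 − r)σ²/n, variances 6(1 − r)σ²/n and 4(1 − r)σ²/n. The correlation is 3/√24 = 0.61 for any r.
- Against the between-arm difference at T1 alone: covariance 2(1 − r)σ²/n, variances 6(1 − r)σ²/n and 2σ²/n. The correlation is √((1 − r)/3): 0.41 at r = 0.5, 0.26 at r = 0.8 and 0.18 at r = 0.9.

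A control group that happens to score low at T1 therefore pushes both analyses towards a benefit.

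**The case against.** The strongest reply is that the trial already has a randomised efficacy test and that the control-group analysis sits under its own heading, limited to that group. Ranking analyses as confirmatory or supportive is often left to an analysis plan, which is not shown. That has some force, but the point does not rest on a missing ranking. It rests on the aim that the article does state for a contrast that cannot deliver it.

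Several stronger readings are tempting, and the document does not support them:

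- **That this is a plain before–after test.** It is a difference of two changes within each child, so growth or disease course moving at a constant rate cancels over equal windows.
- **That training is confounded with season.** Blocking to keep the groups balanced throughout the trial suggests staggered entry, and no recruitment calendar is given. The windows may fall at different times of year for different children.
- **That one relapse would produce a false result.** Assume one child of 15 falls by 5 ml/kg/min at T1 and recovers by T2. That adds 2 × 5/15 = 0.67 to the mean, 9% of 7.26. It is about 0.2 to 0.4 standard errors (0.67/3.2 at r = 0.6, 0.67/1.6 at r = 0.9), and the outlier also widens the interval.
- **That test learning could pass as benefit.** A gain at the first retest lowers the contrast. An assumed 3–5% of 33 (0.99 to 1.65) would hide 14–23% of the target.
- **That using T1 twice invalidates the t-test.** Random error at T1 adds variance, not bias. Only a shift shared by the group biases the result.
- **That the plan claims independent replication.** It does not. The overlap matters only for how the two results are read together.

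**Conclusion.** The point holds as a matter of labelling and interpretation. An efficacy aim is given to a fixed-order, non-randomised contrast with no concurrent untrained group. Window effects that are not constant are aliased with training, in either direction, and a group-wide shift at T1 has double weight. For net window effects of 2 ml/kg/min, the false-positive rate would be about 8–21% instead of 5%, or power for 7.26 would fall by about 13 to 27 percentage points across the three correlations shown. The size of any window effect, the correlation and its equality across visits are all assumptions. The document neither shows nor excludes such effects.

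A reader might infer that the trial's efficacy conclusion is compromised. It is not: the randomised T0–T1 comparison does not use T2 and is untouched. The change is worth making because it costs almost nothing, but it is not a flaw in the main result.

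**What to change.** In *Intervention in control group*:

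1. Describe the analysis as supportive and non-randomised, in place of the efficacy aim.
2. State that the efficacy conclusion rests on the randomised T0–T1 comparison in *Intervention group Vs control group*.
3. Report the control group's T0–T1 change and T1–T2 change separately, each with a 95% confidence interval, alongside their difference. A reader can then see whether an apparent effect comes from the training window or from movement during the wait.

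It may be tempting to add a sensitivity analysis without controls who relapsed or changed medication between T0 and T2. I advise against it. It conditions on events after randomisation, would drop children who worsened while training, and could favour training. At most, describe such events by window.

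The cost is a change of wording and two extra intervals from data already collected. The trial gives up a second efficacy claim.

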#### “Wash-out” effect in intervention and control group

Repeated measures ANOVA analyzes will be performed to examine whether the effects of the intervention are maintained after 12 weeks. Specifically, the outcome measures of both groups will be compared between post-12-week usual care after intervention vs. post-intervention and post-12-week usual care after intervention vs. pre-intervention.

Results will be presented as linear regression coefficients representing mean group differences with their corresponding 95% confidence intervals (CI). Statistical significance will be defined as cases in which the 95% CI does not include the null value. Nominal variables will be analyzed using chi-square analysis. All results will be analyzed using the modified intention to treat approach which means that all subjects will be included in the groups to which they are randomized, and the researchers make efforts to obtain outcome data for all subjects, even if they do not complete the full intervention [50].

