### Power calculation

A power calculation was performed based on previously published data relating to one of the primary outcome measures: VO_2peak/kg_. The mean ± standard deviation VO_2peak/kg_ of patients with JDM (in remission) is 33 ± 8 ml·kg^-1^·min^-1^[13]. The aim of this training intervention is to improve VO_2peak/kg_ by at least 22%, which is the weighted mean improvement in exercise training studies in adults with inflammatory myositis [17]. Given an 80% probability of detecting a treatment effect, with significance set at 0.05 (two-tailed), the required number of total subjects is 22; 11 in each of the 2 groups. Upon factoring in a 20% (*n* = 5) chance of missing observations and/or drop-outs, the total sample size increase to 27 patients. For simplicity in the randomization process, we want to include 30 patients.

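### The wash-out ANOVA and the control-group paired t-test drop children who miss a visit they use, which fits poorly with the stated inclusion of all subjects and the 20% missing data expected

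*Protocol article*

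**What the plan says.** The Statistical analysis section of the protocol article sets out three analyses.

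- *Intervention group vs control group*: mixed linear regression at T0 and T1.
- *Intervention in control group*: the changes under usual care, from T0 to T1, "will be compared with the changes in outcome measures between T1 and T2 (intervention) using a paired samples *T*-test".
- *Maintenance of effect*, under the wash-out heading, is to be handled by ANOVA: "Repeated measures ANOVA analyzes will be performed to examine whether the effects of the intervention are maintained after 12 weeks". The comparisons are "post-12-week usual care after intervention vs. post-intervention and post-12-week usual care after intervention vs. pre-intervention".

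The wash-out subsection then gives a rule that is not limited to the randomised comparison: "All results will be analyzed using the modified intention to treat approach which means that all subjects will be included in the groups"; the groups meant are those set by the randomisation. On follow-up of children who stop training early, it says that "the researchers make efforts to obtain outcome data for all subjects, even if they do not complete the full intervention". The Power calculation section allows for a 20% "chance of missing observations and/or drop-outs". The article names no imputation for the second or third analysis.

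**The concern.** The plan expects missing data, states an inclusion rule for all results, and then names for two of its three analyses methods that cannot use a child with an incomplete set of visits. A paired t-test on two change scores has no pair to work with if either change is missing. Repeated-measures ANOVA, as normally run, deletes a subject with any missing occasion.

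Two things are at stake. One is precision, in a trial of 30 children with about 15 controls. The other is validity: complete-case estimates are in general unbiased only if data are missing completely at random, whereas a likelihood-based mixed model needs the weaker missing-at-random assumption. The wash-out effect is a stated aim in both the Background and the Discussion, and it depends on the last visit of each arm.

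**Working it through.** **Inputs.** Planned enrolment 30 and missing-data allowance 20% (Power calculation); 1:1 allocation, so about 15 per group, and the visit schedule (Study design); methods (Statistical analysis).

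**Step 1: visits each analysis needs.** Under Study design the intervention group trains between T0 and T1 and has its last visit at T2. Controls train between T1 and T2 and have their last visit at T3.

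| Analysis | Children | Visits used |
|---|---|---|
| Control-group paired t-test | controls | T0, T1, T2 |
| Wash-out ANOVA | intervention group | T0, T1, T2 |
| Wash-out ANOVA | controls | T1, T2, T3 |

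The t-test quantity is (T2−T1)−(T1−T0) = T2 − 2·T1 + T0, so all three visits enter. T0 can be missing too, because the test battery follows randomisation.

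**Step 2: the plan's own allowance.** 0.20 × 22 = 4.4, rounded up to 5; 22 + 5 = 27; enrolment is then set at 30. The plan's figures reproduce. The text does not say which visits the 20% refers to.

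**Step 3: children remaining under that allowance.** Assume the 20% means children lacking at least one visit the analysis needs.

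- Wash-out: 30 × (1 − 0.20) = 24.
- Control-group paired test: 15 × (1 − 0.20) = 12.

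**Step 4: range under another assumption.** Let each visit be missing independently with probability p. The complete fraction over three visits is (1 − p)³. Relative to complete data, the standard error of a within-child mean difference grows by 1/√fraction.

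| Assumption | Fraction complete | Of 30 | Of 15 | Standard error factor |
|---|---|---|---|---|
| 20% of children lack a needed visit | 0.800 | 24 | 12 | 1.12 |
| p = 5% | 0.857 | 25.7 | 12.9 | 1.08 |
| p = 10% | 0.729 | 21.9 | 10.9 | 1.17 |
| p = 20% | 0.512 | 15.4 | 7.7 | 1.40 |

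If T0 is complete and p = 10% at the two later visits, the fraction is 0.9² = 0.81, again about 12 of 15 controls. The last column compares with complete data, so it is an upper limit on what another method could recover.

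**Step 5: what a mixed model would keep.** Every child with at least one measured visit contributes the visits that exist. With complete data, a model with a separate mean for each group-by-visit cell gives the same point estimates as the paired differences. The planned comparisons are therefore unchanged; only the handling of incomplete children differs.

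**The case against.** The best defence is that the inclusion rule is softer than it looks. It is called modified intention to treat, it speaks of the randomised groups, and it commits the researchers to efforts rather than to complete data. Read that way, it means analyse as randomised and pursue outcomes whatever the adherence. An analysis plan that is not shown could also add imputation. This stands in part: the text is a poor fit between rule and methods rather than a proven contradiction. Still, efforts do not guarantee data, the rule is worded for all results, and the article itself fixes the methods.

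The follow-up comparisons could also be run pairwise, so that each needs only two visits. That would rescue a child missing only the third visit. A child without the follow-up visit would still be lost from both comparisons.

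A reader might infer more than the documents support:

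- *Any missed visit removes a child.* No. A control missing only T3 stays in the paired t-test, and a control missing only T0 stays in the wash-out analysis.
- *Complete-case results overstate maintenance or the training effect.* The direction is not shown. Children who do poorly may stay away, but children who are well may also skip follow-up, and the commitment to pursue non-completers works against such selection.
- *The planned presentation as regression coefficients rules these methods out.* That sentence concerns mean group differences, which fits the between-group regression. A paired t-test also gives a mean difference with a confidence interval.
- *The main efficacy result is compromised.* It is not; that comparison uses mixed regression.

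**Conclusion.** The point holds for the wash-out and within-control analyses only. As conventionally run, the named methods exclude children whom the inclusion rule, on its plain wording, would include, and the protocol expects such children. On the protocol's own 20%, about 6 of 30 children drop out of the wash-out analysis and about 3 of 15 out of the control-group analysis, with a standard error up to about 12% larger than with complete data. This rests on three assumptions: the 20% refers to children lacking a needed visit, the groups are about equal in size, and no imputation is specified elsewhere. Any bias is possible but of unknown direction. The change is worth making because a better-suited method is already in the plan.

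**What to change.** For both analyses, replace the ANOVA and the t-test by the mixed linear regression already named for the group comparison. Fit one model per outcome with all available visits, group-by-visit as categorical fixed effects, and within-child correlation. The intervention group has no T3 by design, so that cell does not exist and is not missing data. Report these linear contrasts with 95% confidence intervals:

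- control-group effect: (T2−T1)−(T1−T0) in controls;
- wash-out, intervention group: T2−T1 and T2−T0;
- wash-out, controls: T3−T2 and T3−T1.

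T0 and T1 must stay separate levels. A factor that merges them as usual care cannot give the control-group contrast, which weights T0 by +1 and T1 by −2.

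If the sponsor prefers to keep the named methods, the minimum is one sentence that labels them complete-case analyses and exempts them from the inclusion rule.

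The cost is a few lines of analysis text and slightly more modelling work, with no change to visits or data collection. The downside is reliance on missing at random, with a within-child covariance to be estimated from about 30 children.

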**Methods/design:**

Subjects (*n* = 30) will include 8–18 year olds diagnosed with JDM. The intervention consists of an individually tailored 12-weeks home-based exercise training program in which interval training on a treadmill is alternated with strength training during each session. The program is based on previous literature and designed with a defined frequency, intensity, time, and type of exercise (FITT principles). Primary outcome measures include aerobic exercise capacity, isometric muscle strength, and perception of fatigue. The study methodology has been conceived according to the standards of the CONSORT guidelines. The current study will be a multi-center (4 Dutch University Medical Centers) RCT, with the control group also entering the training arm directly after completion of the initial protocol. Randomization is stratified according to age and gender.

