Visual Analogue Scale global disease severity [cm]	na	0-10	-
**Physical activity***(Actical accelerometer for 7 days)*			
	na	>0	+
**Physical activity***(Activity journal for 2 weekdays + 1 Saturday)*			
Time inactive [%]	na	0-100	-
Time light active [%]	na	0-100	−/+
Time moderate active [%]	na	0-100	−/+
Time vigorous active [%]	na	0-100	+

Abbreviation: na: not applicable.

^1^ the primary outcome measure on which power calculation was performed.

+: an increase in value denotes an improvement -: a decrease in value denotes an improvement.

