### Primary study outcomes

*Aerobic exercise capacity* will be measured with a treadmill-based (RAM, Accuramed BVBA, Lummen, Belgium) incremental maximal exercise test according the protocol set out by the German Society for Pediatric Cardiology [33]. Briefly, the test starts at a speed of 2 km·h^-1^ with a 0% grade; the speed increases by 0.5 km·h^-1^ and the grade by 3%, up to a maximum of 21%, every 90 s. The test is terminated upon voluntary exhaustion, despite strong verbal encouragement.

Throughout the test, the subject will wear a facemask (Hans Rudolph Inc, Kansas City, MO) connected to a gas analysis system (ZAN 600, Accuramed BVBA, Lummen, Belgium), which will allow for a sample of expired gases to pass to a flowmeter, an oxygen analyzer, and a carbon dioxide analyzer. Volume calibration and gas analysis calibration will be performed before each testing session. The flow meter and gas analyzers are connected to a computer that calculate breath-by-breath minute ventilation (VE), oxygen uptake (VO_2_), carbon dioxide output (VCO_2_), and the respiratory exchange ratio (RER = VCO_2_/VO_2_) using conventional equations. HR will be measured continuously via a 12-lead electrocardiogram (CardioPerfect, IT medical, the Netherlands). The test will be deemed maximal when the HR is >180 beats·min^-1^ and/or the RER >1.0.

The outcome measures related to aerobic exercise capacity that will be assessed include: VO_2peak_ [l·min^-1^]: the average volume of the absolute oxygen uptake during the last 30-s period of the test; VO_2peak/kg_ [ml·kg^-1^·min^-1^]: the absolute VO_2peak_ divided by body mass. This variable was used for the power calculation; VO_2VAT_ [l·min^-1^]: the absolute VO_2_ eliciting the ventilatory anaerobic threshold (VAT). The VAT will be determined as defined by an increase in both the ventilatory equivalent of oxygen (=VE/VO_2_) and end-tidal pressure of oxygen with no concurrent increase in the ventilatory equivalent of carbon dioxide (=VE/VCO_2_); VO_2VAT/kg_ [ml·kg^-1^·min^-1^]: the absolute VO_2VAT_ divided by body mass; O_2_ pulse [ml·beat^-1^]; and endurance time [min]: the time from the start to the end of the protocol.

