*Isometric muscle strength* of the proximal muscle groups in the lower extremities will be measured on both the right and left sides with a calibrated CITEC hand-held dynamometer (C.I.T. Technics, Groningen, the Netherlands). Both the extensors of the knee joint and the flexors of the hip joint will be assessed with 3 consecutive measurements according to the ‘break method’, wherein the examiner gradually overcomes the muscle force and stops at the moment the extremity gives way [34]. The highest value of the 3 repetitions will be recorded. All within-subject tests will be performed by the same assessor using the same hand-held dynamometer to prevent inter-observer and inter-instrument bias [34].

*Perception of fatigue* will be measured with the Dutch translated PedsQL Multidimensional Fatigue Scale. This scale, designed to measure fatigue in pediatric patients, reflects 3 subscales: general fatigue, sleep/rest fatigue, and cognitive fatigue [35-37].

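### Fourteen measures carry primary status, each with its own unadjusted 95% CI rule and none named as deciding, so a primary efficacy claim is not held to a 5% error rate

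*Protocol article*

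**What the plan says.** All references are to the protocol article.

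- **Primary domains.** Abstract, *Methods/design*: "Primary outcome measures include aerobic exercise capacity, isometric muscle strength, and perception of fatigue".
- **Aerobic measures.** *Primary study outcomes* introduces a list with "The outcome measures related to aerobic exercise capacity that will be assessed include: VO_2peak" and continues with VO2peak/kg, VO2 at the ventilatory threshold (absolute and per kg), O2 pulse and endurance time. Table 2 has the same six.
- **Strength measures.** The same section says "Both the extensors of the knee joint and the flexors of the hip joint will be assessed with 3 consecutive measurements", and that strength "will be measured on both the right and left sides". Table 2 lists the four muscle-and-side combinations as four outcomes.
- **Fatigue measures.** The scale "reflects 3 subscales: general fatigue, sleep/rest fatigue, and cognitive fatigue". Table 2 adds the total score, making four.
- **Analysis.** *Intervention group Vs control group* takes the group as independent variable "and the outcome measures (see Table2) as separate dependent variables".
- **Significance.** "Statistical significance will be defined as cases in which the 95% CI does not include the null value". The sentence stands under the wash-out heading. The sentence before it speaks of regression coefficients for group differences, so the rule covers the randomised comparison.
- **Status of VO2peak/kg.** *Power calculation* describes it as one among the primary measures. The Table 2 footnote marks it as "the primary outcome measure on which power calculation was performed". Alpha there is 0.05 two-tailed and is not shared among the primaries.

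**The concern.** A 5% error rate attaches to one test. Here 14 tests share the primary label and each is judged at 5%, with nothing to say which of them, or how many, must succeed before the trial can be called positive for efficacy. The *Discussion* presents the study as the first randomised trial of exercise training in this disease and as a source of evidence on efficacy. With about 30 children, an isolated result on one muscle group on one side, or on one fatigue subscale, could be reported as a positive primary outcome without departing from anything in the published plan. The error rate behind such a claim would be unknown and well above 5%.

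**Working it through.** **Count.** Aerobic 6 + strength 4 (2 muscle groups × 2 sides) + fatigue 4 (total + 3 subscales) = 14. The text of *Primary study outcomes* and Table 2 agree.

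**Per-test level.** A 95% CI that excludes the null is a two-sided test at 0.05.

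**Independent tests.** The chance of at least one false positive among k tests is 1 − 0.95^k.

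- k = 14: 1 − 0.95^14 = 1 − 0.488 = 0.512
- k = 3 (one measure per domain): 1 − 0.95^3 = 1 − 0.857 = 0.143

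**Correlated tests.** The measures are clearly correlated: absolute and per-kg uptake, right and left limbs, total and subscales. The documents give no correlations, so those below are assumptions. I simulated trials with no treatment effect, 15 per arm, a two-sample t-test on each measure and 100,000 trials per setting, and counted trials with at least one p < 0.05.

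| Assumed correlation | At least one false primary result |
|---|---|
| All 14 equally correlated, 0.3 | 44% |
| All 14, 0.5 | 36% |
| All 14, 0.7 | 26% |
| All 14, 0.8 | 20% |
| All 14, 0.9 | 14.6% |
| 0.5 within domain, 0.2 between | 43% |
| 0.7 within, 0.2 between | 36% |
| 0.8 within, 0.2 between | 32% |
| 0.9 within, 0.3 between | 26% |
| 0.9 within, 0.5 between | 24% |
| Three measures only, 0.5 | 13% |

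The lowest 14-measure figure needs a correlation of 0.9 between, for example, hip flexor force and cognitive fatigue, which is hard to believe. It is still about three times the nominal level.

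**Not counted.** The T0 comparison, the paired tests within the control group, the wash-out analyses and all secondary outcomes.

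**Power, for the cost of a remedy.** Inputs from *Power calculation*: mean 33, SD 8, improvement 22%. Difference = 0.22 × 33 = 7.26, and standardised difference = 7.26/8 = 0.9075. I could not reproduce the stated 11 per group from these inputs. The normal approximation for two means gives 2 × (8 × (1.960 + 0.842)/7.26)² = 19.1, so 20 per arm. Eleven per arm would need something unstated, such as baseline adjustment with a correlation of about 0.65. That is a separate matter, but it means the powers below are those of an unadjusted two-sample t-test on the stated SD.

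| Level for VO2peak/kg | 15 per arm | 12 per arm (20% loss: 15 × 0.8) |
|---|---|---|
| 0.05 | 67% | 57% |
| 0.05/3 = 0.0167 | 49% | 38% |
| 0.05/14 = 0.0036 | 27% | 18% |

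**The case against.** A reader might infer that the plan declares the trial positive if any one of the 14 measures is significant. The text does not say that. It defines when a single coefficient is significant and sets no criterion for trial success, whether any or all. The family-wise figures therefore describe what follows if any positive measure is reported as a positive primary outcome. The plan does not prescribe that reading, but it does not prevent it either.

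A second defence is that this is a condensed article and a hierarchy may sit in an analysis plan that is not shown. That is only partly an answer. The article itself fixes the per-measure threshold and the primary label, so a later hierarchy would have to override published wording.

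A third is that VO2peak/kg is the implied sole primary. *Power calculation* rules this out by calling it one of several.

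A reader might also infer that the deciding outcome can be picked freely after the data are seen. That goes too far. Table 2 lists every measure in advance, results are to be given as differences with CIs, and assessors and analysts are to be blinded. These limit hidden selection, but they do not control the error rate.

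Finally, 51% is not a realistic estimate, because the measures are not independent. This stands, and the figure is given as the independence value only.

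**Conclusion.** The point holds in conditional form. The article labels 14 measures primary, tests each separately at an unadjusted 5% and supplies no deciding measure, joint-success rule or alpha split. If any positive one is taken as a positive primary outcome, the chance of at least one false primary result is 51% under independence and roughly 15% to 44% across the assumed correlations. With one independent measure per domain it is 14%. The count and the independence figures follow directly from the document. The 15–44% range depends on correlations that the document does not give, but every setting tried lies well above 5%. Because this governs the trial's main efficacy conclusion, it needs to be settled before results are seen.

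**What to change.** Name VO2peak/kg at T1, the randomised comparison, as the single primary endpoint at two-sided 0.05. Report the other 13 measures as secondary, as estimates with 95% CIs, and state that none of them alone supports a primary efficacy claim. The sample-size basis is unchanged, no patients or assessments are added, and the primary claim carries a 5% error rate.

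If the team wants confirmatory claims on strength and fatigue, it should pre-specify one existing Table 2 measure per domain (for example the fatigue total score) and a multiplicity rule such as a fixed sequence or Holm. That choice belongs to the team, and neither rule is free:

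- **Fixed sequence with VO2peak/kg first.** On the stated inputs VO2peak/kg has about 67% power at 15 per arm, or 57% at 12. Strength and fatigue would then go formally untested in about 33% to 43% of trials, even if the assumed aerobic effect is real.
- **Holm over three.** The three domains stay parallel, but the first step is at 0.05/3, where VO2peak/kg has about 49% power at 15 per arm.

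Adjusting across all 14 would cut that to about 27% and is not a practical choice. The cost of the main fix is that strength and fatigue, which the article presents as major clinical concerns, lose free-standing primary status.
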